**LIST OF ABBREVIATIONS**

|              |                                                  |
|--------------|--------------------------------------------------|
| ART          | Antiretroviral Therapy                           |
| BMI          | Body mass index                                  |
| DAT          | Direct agglutination test                        |
| DND i | Drugs for Neglected Diseases Initiative          |
| HIV          | Human immunodeficiency virus                     |
| LHR          | Likelihood ratio                                 |
| LRTC         | Leishmania Research and Treatment Centre         |
| ITM          | Institute of Tropical Medicine, Antwerp, Belgium |
| IRB          | Institutional Review Board                       |
| MSFH         | Médecins Sans Frontières Holland                 |
| PhD          | Doctor of Philosophy                             |
| PI           | Principal Investigator                           |
| ROC          | Receiver operating characteristic curve          |
| TB           | Tuberculosis                                     |
| VL           | Visceral Leishmaniasis                           |

## SUMMARY

**Title:** Clinical prognostic tools for mortality in visceral leishmaniasis in a high HIV co-infection burden area in Ethiopia

### Primary objective

To develop a mortality prognostic score for visceral Leishmaniasis (VL) patients with an area under the receiver operating characteristic curve (ROC) of more than 0.75.

### Secondary objective

1. To determine the predictive factors for mortality in VL patients.
2. To determine the predictive factors for mortality in VL-HIV co-infected patients.

### Tertiary Objective

To develop a mortality prognostic score for VL-HIV co-infected patients with an area under the receiver operating characteristic curve (ROC) of more than 0.75.

### Study design

A retrospective cohort analysis using prospectively collected standardized program data.

### Study setting

Development of the tool: Abdurafi health centre in Abdurafi (Ethiopia) supported by Médecins Sans Frontières Holland.

External validation of the tool: Leishmania Research and Treatment Center at the University of Gondar Hospital supported by the Drugs for Neglected Diseases Initiative.

### Study population

Development of the tool: All patients diagnosed with primary and relapse VL between January 2008 to December 2013.

External validation of the tool: All patients diagnosed with primary and relapse VL between January 2011 to December 2012.

### Sample Size

1. Development of the score:

All VL patients: VL patients diagnosed between January 2008 to December 2013. There were 1729 patients diagnosed in this period among whom 99 died.

VL-HIV co-infected patients. VL patients diagnosed between January 2008 to December 2013. There were 345 patients diagnosed in this period among whom 51 died.

2. External validation:

All VL patients: VL patients diagnosed between January 2011 to December 2012. There were 526 patients diagnosed in this period among whom 53 died.

VL-HIV co-infected patients. VL patients diagnosed between January 2011 to December 2012. There were 55 patients diagnosed in this period among whom 28 died.

## **Main outcome**

In health-centre/hospital mortality

## **Inclusion criteria**

1. Cured patients
2. Dead Patients

## **Exclusion criteria**

1. Transferred patients
2. Defaulted patients

The transferred and defaulted patients were few (approximately 4%). Additionally, patients with treatment failure were excluded from the external validation cohort. There were no patients with treatment failure in the derivation cohort.

## **Study variables**

The following variables will be collected and analyzed. They are identified by literature review for predictive factors for mortality and consideration of routinely collected program data

- Demographics: age, sex
- Clinical
  - o On admission:
    - Duration of illness
    - Presence or absence of weakness, ascites, peripheral edema, bleeding, jaundice, tuberculosis
    - Spleen size
    - Body mass Index (BMI)
    - Hemoglobin
- VL history (Primary VL versus VL relapse); VL treatment received
- HIV status, Antiretroviral use, CD4+ T lymphocyte count

## **Statistical methods**

Statistical analysis will be done with Stata version 13.1. The main exposure variables in 10% of the patient charts will be validated against the records in the excel database. Univariate and multivariate logistic regression analysis will be done. The Spiegelhalter and Knill Jones method will be used to develop the score. Predictors with an adjusted likelihood ratio of  $\leq 0.67$  and  $\geq 1.5$  will be used to develop the score. A receiver operating characteristic curve will be constructed and cut off selected with the Zweig and Campbell formula.

## **Main results**

1. The predictive factors for mortality in VL patients.

2. The predictive factors for mortality in VL-HIV co-infected patients.
3. The performance of the prognostic score in VL patients as per receiver operating characteristic curve with sensitivity, specificity, predictive values and likelihood ratios at different cut-offs of the score.
4. The performance of the prognostic score in VL-HIV co-infected patients as per receiver operating characteristic curve and with sensitivity, specificity, predictive values at different cut-offs of the score.
5. A clinical algorithm identifying groups of VL patients with varying risk of mortality.
6. A clinical algorithm identifying groups of VL-HIV co-infected patients with varying risk of mortality.

### **Possible limitations**

1. The clinical records of critical patients may contain more complete data compared to the rest of the patients thus creating some bias.
2. There will be some missing data however they are few (<1%). Médecins Sans Frontières Holland has multi-country standardized data collection tools (See Annexe 1). Standardized data collection forms were used to collect the data at the Leishmania Research and Treatment Centre.
3. The definition of the variable “weakness” is not based on the Karnofsky performance scale Index or standardised system at both VL treatment sites.

### **Impact**

Once validated it can help identify patients at high risk of mortality, who might benefit more from the more expensive and less accessible AmBisome; and from intensive monitoring by the scarce human resources; it can help in the decentralization of care by deciding which patients may be treated in the hospital and which ones treated in the health centre and lastly, it may play a role in selection of patients to target groups in future studies.

## 1. INTRODUCTION

### 1.1 Background

Visceral Leishmaniasis (VL) or Kala-azar is a disseminated protozoan infection caused by *Leishmania donovani* species complex and transmitted through the bite of the female sandfly. The anthroponotic form is caused by *L. donovani* and is the most prevalent. It occurs in East Africa, Bangladesh, India and Nepal. The zoonotic form with dogs as the main reservoir is caused by *L. infantum* and occurs in the Mediterranean basin, China, the Middle East and South America. VL is present in more than 70 countries and 200 million people are at risk. Annually there are 500,000 new cases and 50,000 deaths. 90% of VL cases occur in only 6 countries namely Bangladesh, Brazil, Ethiopia, India, Nepal and Sudan. In Ethiopia, 2000-4500 VL cases occur annually.

Human immunodeficiency virus (HIV) is one of the main risk factors for VL and consequently the HIV epidemic has significantly increased VL caseloads especially in East Africa. In Ethiopia, HIV prevalence among VL patients is 20-40%, the highest co-infection rate in the world. VL and HIV are both immunosuppressive and act synergistically with detrimental effects. Co-infected patients show atypical presentation, have several VL relapses, higher rates of drug toxicity, treatment failure and mortality. The high treatment failure rates are a risk factor for the development of drug resistance.

VL is fatal without treatment and the main drugs used for treatment are antimonials and Liposomal Amphotericin B (AmBisome). Sodium Stibogluconate is a commonly used antimonial and a full course of treatment costs 56 US dollars while a course of AmBisome is 13 times more expensive. Antimonials are more toxic than AmBisome especially in HIV co-infected patients, the mortality rate among VL-HIV co-infected patients on antimonial therapy varies from 6.8-33%. This is 4-10 times higher than in non HIV infected patients. However their favourable cost makes them the first choice of treatment in resource limited settings. Although antiretroviral treatment (ART) has been gradually introduced in Ethiopia as well, the epidemiological and clinical impact on VL-HIV co-infection has been poorly documented.

### 1.2 Rationale

The optimal management of severe cases remains poorly identified and is highly variable across physicians and treatment sites. A critical factor that could contribute in reducing adverse outcomes include the availability of evidence-based prognostic tools. Such tools are increasingly used in stratified or risk-based medicine, to identify the individuals requiring close observation, and additional testing or treatment. On the other hand, individuals with an excellent prognosis might be treated in an ambulatory way or at the decentralized level.

To be clinically relevant and influence clinical care or VL programs, identified prognostic factors should be integrated in easy to use tools. For instance, clinical prognostic tools or prediction scores have been developed to predict mortality or morbidity in HIV infected patients, relying on easy to measure clinical and laboratory information. While a scoring system for VL mortality has been developed in Sudan, it has never been validated. Moreover, it was developed over ten years ago within a specific setting in South Sudan; it is however not known to what extent it is applicable to the Ethiopian setting, with high HIV co-infection rates.

Using standardized VL program data from a high VL-HIV burden setting, we aim to identify independent risk factors associated with death in VL patients and **to develop and externally validate a clinical prediction score for VL mortality**. Such a tool could contribute to reducing

VL case fatality by allowing the early identification of patients at higher risk for death from VL, and to implement focused strategies. A validated clinical prediction score could help identify patients at high risk of mortality, who might benefit more from the scarcely available AmBisome, intensive monitoring by the scarce human resources; it can help in the decentralization of care by deciding which patients may be treated in the hospital and which ones treated in the health centre and lastly, it may play a role in selection of patients to target groups in future studies. Clinical prediction scores are potentially highly useful tools but their study for use in resource limited settings is very limited. Our studies will be one of the few dedicated to this.

## **2. STUDY DESIGN**

This is a retrospective cohort study using prospectively collected standardized program data. It is foreseen to last for 7 months.

## **3. STUDY OBJECTIVES**

### **3.1 Primary Objective**

To develop a mortality prognostic score for VL patients with an area under the receiver operating characteristic curve (ROC) of more than 0.75.

### **3.2 Secondary Objective**

1. To determine the predictive factors for mortality in VL patients.
2. To determine the predictive factors for mortality in VL-HIV co-infected patients.

### **3.3 Tertiary Objective**

To develop a mortality prognostic score for VL-HIV co-infected patients with an area under the receiver operating characteristic curve (ROC) of more than 0.75.

### **3.4 The expected outcomes**

1. The predictive factors for mortality in VL patients.
2. The predictive factors for mortality in VL-HIV co-infected patients.
3. The performance of the prognostic score in VL patients as per ROC and with sensitivity, specificity, predictive values at different cut-offs of the score.
4. The performance of the prognostic score in VL-HIV co-infected patients as per ROC and with sensitivity, specificity, predictive values at different cut-offs of the score.
5. A clinical algorithm identifying groups of VL patients with varying risk of mortality.
6. A clinical algorithm identifying groups of VL-HIV co-infected patients with varying risk of mortality.

## 4. METHODS

### 4.1 Study Setting

**Development of the tool** will be conducted in Abdurafi Health centre in Abdurafi town, West-Armacheo district, North West Ethiopia. It is a poor and remote district with poor access to health. It has one of the highest burden of VL and HIV in Ethiopia. Seasonal crop farming is one of the main activities and approximately 300,000 migrant workers travel in and out of the region seasonally. Commercial sex work is also very common.

The health centre belongs to the Ethiopian bureau of health and has been supported by Médecins Sans Frontières Holland (MSFH) since 2004. It focusses on the clinical management of VL, HIV and concomitant infections. It is one of the main VL treatment sites in Ethiopia and medical services are free of charge. The majority of the patients treated are migrant workers.

We consider this site suitable for our study because of the following facts:

- (1) Ethiopia is one of the top six countries in the world with the highest burden of VL and it has the highest burden of VL-HIV Co-infection.
- (2) Readily available high quality data: Since the VL program onset in 2004, standardized data collection sheets (patient cards) have been used, from which data are transferred to an electronic database. (See Annex 1) Clinical teams are trained on standardized clinical procedures and data collection and a data quality system is in place.
- (3) The VL mortality rate remains high in the health center.

**External validation of the tool** will be conducted at the Leishmania Research and Treatment Center (LRTC) at the University of Gondar Hospital supported by the Drugs for Neglected Diseases Initiative (DNDi). The LRTC is located in Gondar city and is the main referral facility for critically ill or complicated VL cases. The main focus for this centre, is the clinical management of VL and concomitant infections and clinical research on VL. It is one of the main VL treatment sites in the high HIV co-infection burden area and medical services are free of charge. We consider this site suitable because along with Abdurafi health centre they are the main VL treatment sites in the high HIV co-infection burden area. Furthermore there is readily available high quality data collected using standardized data collection forms.

### 4.2 Population

**Development of the tool:** All patients diagnosed with primary and relapse VL between January 2008 to December 2013.

**External validation of the tool:** All patients diagnosed with primary and relapse VL between January 2011 and December 2012

### 4.3 Sample Size

#### Development of the tool:

**All VL patients:** The score will be developed on the 1729 patients diagnosed between January 2008 to December 2013, among whom 99 died. According to a rule of thumb, ten deaths are required for each parameter in the logistic regression model. Therefore the final model should

contain no more than 9 parameters. Five-fold cross validation will be performed to evaluate the performance of the score.

**VL-HIV co-infected patients.** VL Patients diagnosed between January 2008 to December 2013. There were 345 patients diagnosed in this period among whom 51 died. Therefore the final model should contain no more than 5 parameters. Five-fold cross validation will be performed to evaluate the performance of the score.

#### **External validation of the tool:**

**All VL patients:** The sample size will be pre-determined by the available data (53 deaths).

**VL-HIV co-infected patients:** The sample size will be pre-determined by the available data (28 deaths)

#### **4.4 Main outcome**

The main outcome measured is mortality during VL treatment (In-health centre/hospital mortality).

#### **4.5 Inclusion Criteria**

In the derivation and external validation cohort, we will include all patients with the outcomes mentioned below.

1. Cured
2. Dead

#### **4.6 Exclusion Criteria**

In the derivation and external validation cohort, we will exclude all patients with the outcomes mentioned below.

1. Transferred
2. Defaulted

The transferred and defaulted patients were few (approximately 4%). Additionally in the external validation cohort, we will exclude all patients with treatment failure. There were no patients with treatment failure in the derivation cohort.

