#### **Definitions of outcome variables:**

- **Death:** Death during VL treatment at the health center.
- **Cure:** Improvement in symptoms and signs of VL 20-30 days after VL treatment initiation i.e. absence of fever, decrease in spleen size, increase in haemoglobin level, weight gain and a negative test of cure (parasitological test) where indicated.
- **Transfer:** A VL patient on treatment that is sent to a higher level health facility for better management or sent to another health facility for compassionate reasons e.g. proximity of that health facility to the patients' home.
- **Defaulter:** A VL patient on treatment that absconds from treatment and does not return or returns but the VL treatment has to be restarted from the first day.
- **Treatment failure:** It is defined as a positive parasitological test at the end of VL treatment.

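### Transferred and defaulted patients are excluded by outcome and justified only as few, yet they number about 70% of the deaths and the exclusion may be informative

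*Protocol*

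**What the plan says.** Protocol section 4.5 admits only patients whose outcome was cure or death. Section 4.6 states the counterpart: "In the derivation and external validation cohort, we will exclude all patients with the outcomes mentioned below", naming transfer and default. The justification is "The transferred and defaulted patients were few (approximately 4" percent). No denominator, breakdown by cohort or split between the two reasons accompanies that figure. (The validation cohort also drops treatment failures, which is not the subject here.)

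The outcome definitions in section 4.7.2 give transfer two routes. One is being "sent to a higher level health facility for better management". The other is a move on compassionate grounds, such as being nearer home. A defaulter is someone who absconds and stays away, or who comes back but must begin treatment again. Death counts only if it happens during VL treatment at the centre.

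On numbers, section 4.2 defines the derivation population as "All patients diagnosed with primary and relapse VL between January 2008 to December 2013", and section 4.3 says "The score will be developed on the 1729 patients diagnosed between January 2008 to December 2013, among whom 99 died". The Summary has the same count: "There were 1729 patients diagnosed in this period among whom 99 died". The limitations listed in the Summary do not mention the exclusion.

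**The concern.** A score applied at admission is meant for everyone admitted. Choosing the derivation patients by exit status conditions on something the user of the score cannot know. That does little harm if the excluded group is small relative to the information in the data and its exit is unrelated to prognosis. The protocol argues only the first of these, and against the wrong yardstick. With an event rate near 6%, the information lies in the deaths, so the size of the excluded group should be judged against them.

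The second condition is doubtful on the protocol's own definition, because one route to transfer is the need for better care. The intended use makes this matter more. Section 1.2 and the Summary's impact statement say the score should help decide who is treated in hospital and who in the health centre, and some of the excluded patients are those for whom such a decision was actually made.

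Section 4.8.2 keeps predictors at fixed likelihood-ratio thresholds (1.5 and 0.67) and rounds the natural log of the adjusted ratio to an integer. A modest shift can therefore change a point value or whether a predictor stays in.

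**Working it through.** **Inputs.** From section 4.3: 1729 patients, 99 deaths, and the rule that "ten deaths are required for each parameter in the logistic regression model"; 345 patients and 51 deaths with HIV co-infection. From section 4.6: about 4% transferred or defaulted. From the Summary: 526 patients and 53 deaths in the validation cohort. Fatality among the excluded is not given and is an assumption throughout.

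**The plan's own figures.** 99/10 = 9.9, so at most 9 parameters; 51/10 = 5.1, so at most 5. Both reproduce. Neither depends on how 1729 was counted, because excluded patients contribute no recorded deaths.

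**Number excluded.**
- If 1729 is before exclusion: 0.04 × 1729 = 69.2, about 69 excluded and 1729 − 69 = 1660 analysed. Case fatality moves from 99/1729 = 5.7% to 99/1660 = 6.0%.
- If 1729 is after exclusion: 1729/0.96 = 1801 diagnosed, so 1801 − 1729 = 72 excluded, and 1729 stands.
- Reading approximately 4% as 3.5% to 4.5% gives 61 to 78 excluded (before) or 63 to 81 (after).

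**Against the events.** 69/99 = 70%; 72/99 = 73%. If the same 4% held elsewhere, which the protocol does not say, it would be 0.04 × 345 = 14 patients against 51 deaths in the co-infected derivation group, and 0.04 × 526 = 21 against 53 in the validation cohort.

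**Unobserved deaths, by assumed fatality among 69 excluded.**

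| Assumed fatality | Unobserved deaths | Share of all deaths |
|---|---|---|
| 5.7% (cohort average) | 4.0 | 4.0/103.0 = 4% |
| 10% | 6.9 | 6.9/105.9 = 7% |
| 20% | 13.8 | 13.8/112.8 = 12% |
| 33% | 22.8 | 22.8/121.8 = 19% |
| 50% | 34.5 | 34.5/133.5 = 26% |

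With 72 excluded the range is 4.1 to 36.

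**Can it move a score point, and which way?** This illustration uses crude ratios and assumed inputs. Suppose a sign is present in 40% of deaths and 10% of survivors. The ratio is 4.0 and ln 4.0 = 1.39, giving 1 point.
- Add 35 deaths among the excluded, 60% with the sign, and let the excluded survivors resemble other survivors. Deaths with the sign: (0.40 × 99 + 0.60 × 35)/134 = 60.6/134 = 45.2%. The ratio is 4.52 and ln = 1.51, giving 2 points.
- Instead let all 69 survive, 60% with the sign. Survivors observed: 1660 − 99 = 1561. Survivors with the sign: (0.10 × 1561 + 0.60 × 69)/1630 = 197.5/1630 = 12.1%. The ratio is 0.40/0.121 = 3.3 and ln = 1.19, giving 1 point.

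The first case was chosen near a rounding boundary. The pair shows that the ratio can shift either way, not that it will.

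**The case against.** The strongest reply is that nothing here demonstrates bias. The 4% pools transfers for better management, compassionate transfers and defaulters in unknown proportions. Excluded patients leave both numerator and denominator and are not counted as survivors. A predictor is weakened only if excluded patients with the sign died more often than retained patients with it; if they died less often, its weight is inflated. The ratio of 69 to 99 measures group size, not bias. All of this stands, and it limits what can be claimed.

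It is also fair that a death after transfer is not the outcome in sections 4.4 and 4.7.2. Transfer is therefore better called a competing event than lost follow-up of the defined outcome. That does not remove the problem, because the score is intended for all admitted patients, including those who will be transferred.

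A reader might infer that the count of 1729 is simply wrong because it ignores the exclusion. The wording about patients diagnosed points that way if read literally, but 1729 may already be cured plus dead under loose phrasing, and the protocol does not settle it.

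A reader might also infer that the derivation site sends its sickest patients to the validation site, so that the bias differs between cohorts. Section 4.1 calls the validation site the main referral facility for severe cases, but no section says that transfers went there, and the 4% is not given by cohort.

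Finally, sensitivity analyses often sit in a statistical analysis plan, so their absence here is not the defect. The exclusion rule and its justification are fixed in the protocol and can be judged there.

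**Conclusion.** The concern holds in a limited form. Selection by exit status is justified only by a percentage of the whole cohort. The excluded group is about 69 to 72 patients, 70-73% of the number of deaths, and by definition it includes some sent up for better management, so the exclusion may be informative. These counts assume that the 4% applies to the derivation cohort.

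The documents do not show that deaths among the sickest were lost, nor that predictor weights are diluted. About 4 to 35 unobserved deaths is a range under assumed fatality of 5.7% to 50%, and the direction of any effect on the weights is open. The derivation count is ambiguous, with little numerical effect (1660 or 1729 analysed) and none on the 99 deaths or the nine-parameter limit. This is worth correcting because the check is cheap and bears on what the score can claim for all admitted patients.

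**What to change.** 1. In sections 4.2 and 4.3, state whether 1729 is before or after exclusion, and give the analysed number.
2. In section 4.6, report transfers (by reason, if recorded) and defaulters separately for each cohort, and tabulate their admission predictors beside those of included patients.
3. Keep the main analysis and refit the score under two bounds: (a) transfers for better management counted as deaths, or all transfers if the reason was not recorded, with the other excluded patients as survivors; (b) all excluded patients counted as survivors. Report retained predictors, weights and AUC beside the main result. The bounds test sensitivity to the fate of transferred patients; they do not cover deaths among defaulters.
4. Add the exclusion to the stated limitations.

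The cost is one table and two model runs, provided the excluded patients' admission data are in the program database, which the protocol does not confirm. The visible part of the treatment card in Annex 1 shows exit date and location but no reason for transfer, so the fallback in (a) may be needed. The drawback is that the score may look less stable.

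### Section 4.6 drops treatment failures from the external validation cohort although they survived treatment, which raises validation mortality and, if any of them score positive, PPV

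*Protocol*

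**What the plan says.** Section 4.4 of the protocol fixes the endpoint: "The main outcome measured is mortality during VL treatment", described in the same sentence as mortality in the health centre or hospital. The outcome definitions at the end of section 4.7.2 give death as "Death during VL treatment at the health center". Of treatment failure they say: "It is defined as a positive parasitological test at the end of VL treatment".

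Section 4.5 admits only cured and dead patients to both cohorts. Section 4.6 removes transferred and defaulted patients from both, and adds: "Additionally in the external validation cohort, we will exclude all patients with treatment failure". It then notes: "There were no patients with treatment failure in the derivation cohort". The Summary repeats this rule. Neither place gives a reason for it or a number of failures; the figure of about 4% covers only transfers and defaulters.

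Section 4.2 defines the validation population as every primary or relapse VL patient diagnosed in 2011–2012. The Summary puts this at 526 patients with 53 deaths, of whom 55 with 28 deaths were HIV co-infected. It does not say whether these counts are before or after the exclusions.

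**The concern.** Excluding transfers and defaulters can be defended, because their outcome was not observed. Treatment failures are different. A positive test at the end of treatment means that the patient reached the end of treatment alive, so the answer to the study's question is known: this patient did not die during treatment.

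The score is built mainly from admission findings. Sections 1.2 and the Summary (Impact) intend it for picking out high-risk patients early and for deciding where they are treated. At that moment no clinician can tell who will fail treatment. A validation sample selected on that later status is therefore not the population to which the score will be applied, nor the one that section 4.2 defines. Section 4.8.2 reports PPV, NPV, specificity and AUC from this sample, so the selection acts directly on the main validation results.

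**Working it through.** **1. Stated counts.** These are observed counts with no formula behind them. They give crude mortality of 53/526 = 10.1% (all VL) and 28/55 = 50.9% (VL-HIV) in validation, and 99/1729 = 5.7% and 51/345 = 14.8% in derivation.

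**2. Direction of the effect.** Let D be deaths, C cured patients and F failures. Let s be sensitivity, p the share of cured patients above the cut-off, and q the share of failures above it. Assume that no excluded failure died in the same admission.

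| Measure | Failures excluded | Failures kept as survivors | Effect of excluding them |
|---|---|---|---|
| Mortality | D/(D+C) | D/(D+C+F) | always raised if F > 0 |
| Sensitivity | s | s | none |
| PPV | sD/(sD+pC) | sD/(sD+pC+qF) | raised if qF > 0 |
| NPV | (1−p)C/[(1−p)C+(1−s)D] | [(1−p)C+(1−q)F]/[(1−p)C+(1−q)F+(1−s)D] | never raised |
| Specificity | 1−p | [(1−p)C+(1−q)F]/(C+F) | raised only if q > p |

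With failures kept, the AUC is the average of the AUC for deaths against cured patients and the AUC for deaths against failures, weighted C to F. Excluding failures therefore overstates it only if deaths are harder to separate from failures than from cured patients.

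**3. Size for mortality.** The number of failures is not in the protocol, so f, their share of the full cohort, is an assumption.

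*If 526 and 55 are counts after exclusion*, F = N·f/(1−f), rounded:

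| f | All VL | VL-HIV |
|---|---|---|
| as stated | 53/526 = 10.1% | 28/55 = 50.9% |
| 2% | 53/537 = 9.9% | 28/56 = 50.0% |
| 5% | 53/554 = 9.6% | 28/58 = 48.3% |
| 10% | 53/584 = 9.1% | 28/61 = 45.9% |
| 20% | 53/658 = 8.1% | 28/69 = 40.6% |
| 30% | 53/751 = 7.1% | 28/79 = 35.4% |

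*If they are counts before exclusion*, F = N·f and the stated percentages are the unselected ones. Exclusion then raises mortality to 53/500 = 10.6%, 53/473 = 11.2% or 53/421 = 12.6% in all VL patients at 5%, 10% or 20% failures. In VL-HIV patients it rises to 28/52 = 53.8%, 28/49 = 57.1% or 28/44 = 63.6%.

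**4. Size for PPV, specificity and NPV.** This is an illustration in the all-VL cohort, with counts taken as after exclusion. It assumes f = 10% (F = 526 × 0.1/0.9 = 58.4), s = 0.80 and p = 0.25. Then sD = 0.80 × 53 = 42.4 and pC = 0.25 × 473 = 118.25. With failures excluded, PPV = 42.4/160.65 = 26.4%, specificity is 75.0% and NPV = 354.75/365.35 = 97.1%.

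| q | PPV, failures kept | Specificity, failures kept |
|---|---|---|
| 0.15 | 25.0% | 76.1% |
| 0.25 | 24.2% | 75.0% |
| 0.40 | 23.0% | 73.4% |
| 0.60 | 21.7% | 71.2% |

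NPV with failures kept is 97.3–97.4%. At q = p = 0.25, where failures score exactly like cured patients, PPV still falls from 26.4% to 24.2% while specificity does not move.

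**The case against.** The strongest reply is that both analysed cohorts follow one openly declared rule, cured versus dead; that score derivation is untouched; and that the error may be small. All three points are fair. At 10% failures, all-VL mortality moves by one percentage point. Sensitivity is unaffected, and NPV is unbiased or conservative, which matters for the stated aim of identifying patients fit for decentralised care. None of this supplies a reason for discarding patients whose outcome is known.

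It may also be said that the survival of failures is not fully settled, because the definitions do not say how a patient is classified who fails and then dies in hospital. That stands, and the coding rule must cover it.

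A reader might infer more than the protocol supports:

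- **That specificity and AUC are inflated.** This requires failures to score higher than cured patients, and no data show that they do.
- **That failures look like deaths and the HIV score suffers most.** Section 1.1 says: "Co-infected patients show atypical presentation, have several VL relapses, higher rates of drug toxicity, treatment failure and mortality". That compares co-infected with other patients. Within the co-infected cohort everyone has HIV, so HIV status cannot make failures resemble deaths there. The statement supports at most a larger share of failures, and so a larger shift in mortality and PPV.
- **That 50.9% against 14.8% co-infected mortality shows the effect.** Section 4.1 describes the validation site as the main referral centre for critically ill or complicated cases, which is another explanation for the contrast.

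**Conclusion.** The exclusion is wrong as written. It removes patients who are non-events under the protocol's own definitions, because of a status unknown at admission, from a population defined as all diagnosed patients. Higher validation mortality follows for any number of failures above zero. Higher PPV follows as soon as one of them scores above the cut-off.

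The size cannot be established, because the number of failures is not reported. Over an assumed 2–30%, with the stated counts taken as after exclusion, the all-VL effect runs from negligible to three percentage points of mortality, and the VL-HIV effect from about one to about fifteen. The PPV figures rest further on illustrative values of sensitivity, of specificity among cured patients, and of how failures score. Overstatement of specificity or AUC remains a possibility that the data must settle.

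**What to change.** 1. Delete the additional exclusion of treatment failures in section 4.6 and in the Summary.
2. In section 4.5 and the Summary, add treatment failure to the outcomes included in the validation cohort, coded as not having died. State that a failure who died in hospital during the same admission counts as a death, in line with the in-facility mortality of section 4.4.
3. Report the number of treatment failures at the validation site by HIV status.
4. State whether 526/53 and 55/28 are before or after exclusions, and restate them on the new basis in the Summary and section 4.3.
5. Keep the cured-versus-dead comparison as a sensitivity analysis. Its difference from the main result will show whether specificity and AUC were affected.

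The cost is a protocol wording change and a recode of existing validation-site records. Patient care and score derivation are not affected. The downside is that reported validation mortality will be lower and PPV may look less favourable.
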